#### Therapeutic mechanism outcomes

Pro-inflammatory cytokines, including interleukin-1 beta (IL-1β), IL-6, and tumor necrosis factor-alpha, will be tested at baseline and the last visit. An altered cytokine balance (that is, a relatively increased pro-inflammatory response and decreased anti-inflammatory response) was found in GAD [13]. Previous clinical study showed that the anxiolytic effects of selective serotonin reuptake inhibitors may depend on their anti-inflammatory effects, proved by the reduced levels of pro-inflammatory cytokines after treatment [14]. Whether SGQR formula also has an effect on the immune balance needs to be investigated. All blood samples will be collected and centralized for tests.

#### Safety outcomes

Safety outcomes involve complete blood count, electrolyte panel, liver and kidney function tests, urinalysis, urine pregnancy test, and electrocardiograph. Safety outcomes will be assessed at screening time and the last visit.

### Adverse events

Adverse reactions will be checked by using the Treatment Emergent Symptom Scale (TESS) at every visit [15]. If any adverse events happen during the treatment period, all details, including the time of occurrence, clinical symptoms and signs, degree, duration, laboratory findings, treatment, outcomes, and causal relationship with the treatment, will be recorded in the case report forms (CRFs). Serious adverse events will be reported to the research ethics committee, which will decide whether any additional measures should be taken.

### Quality control

Before the conduction of the protocol, a range of training will be provided to all the researchers, ensuring a full understanding and mastery of the standard operating procedures. Any change to the protocol should be reported in writing to the primary researcher in Anding Hospital and can be applied only after permission. The quality of CRFs will be regularly supervised by independent investigators in Anding Hospital. Researchers will be notified in a timely fashion if any error exists.

### Sample size calculation

As there is no large randomized controlled trial of SGQR formula for GAD, we referred to the experience of experts in this field. A response rate of 91% for SGQR was assumed. As to buspirone, the response rate was about 75%, according to the literature [16]. In the setting of α = 0.05 and β = 0.2, the sample size was calculated to be 83 in each group. Given a 20% dropout rate, 17 more participants will be required in each group. In total, 200 participants will be enrolled.

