### Randomization and allocation concealment

Eligible participants will be randomly assigned to either the study group or the control group in a ratio of 1:1. A computer-generated random allocation sequence will be produced by an independent statistician using SAS software (SAS Institute, Cary, NC, USA). Based on the allocation sequence, drug packages will be labeled serially. Participants will receive the corresponding drug package in the order of recruitment. The complete random sequence will be kept by the primary researcher in Beijing Anding Hospital. Emergency envelopes containing the random allocation individually will be prepared for each center, which can be unsealed only in the case of serious adverse events.

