### Data management and analysis

CRFs will be entered by two independent researchers and supervised by a third one to ensure accuracy. Data analysis will be performed by statisticians who are blind to the randomization by using SPSS (Statistical Product and Service Solutions) Statistics for Windows, version 20.0 (IBM Corp., Armonk, NY, USA). Continuous variables will be presented as mean and standard deviation, and categorical variables will be presented as frequency or percentage. Demographic data and outcome measurements at baseline will be listed to ensure relatively even baseline levels. A *t* test (if normally distributed) or non-parametric test (if not normally distributed) will be used for continuous variables when conducting baseline comparisons. The repeated measures ANOVA (analysis of variance) will be used when analyzing the primary and secondary outcomes. Chi-squared or non-parametric test will be applied for categorical variables. The analysis of efficacy will be performed in accordance with the intention-to-treat principle. Missing values will be imputed by the last observation carried forward method. Subgroup analysis will be conducted if necessary. A *P* value of less than 0.05 will be considered statistically significant. A mixed-effects model for repeated measures will be performed as a sensitivity analysis of the primary efficacy outcome.

Mid-term date analysis will be conducted after half of the recruitment is finished, and the principal investigator will decide whether any measure should be taken in light of the results. All of the data will be deposited in the platform developed by our team. Anding Hospital will be responsible for the data, and other researchers can have access to the data only after application and permission.

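### The 20% dropout allowance is computed as 83 × 1.2 instead of 83 / 0.8: 100 per group covers 17% dropout, and 20% dropout leaves 80 completers per group rather than 83

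*Protocol article*

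**What the plan says.** The Sample size calculation section of the Protocol article compares two response rates. For the study arm, "A response rate of 91% for SGQR was assumed"; for buspirone it takes about 75% from a cited source. The result follows: "In the setting of α = 0.05 and β = 0.2, the sample size was calculated to be 83 in each group". The allowance for losses comes next: "Given a 20% dropout rate, 17 more participants will be required in each group". This makes 100 per group and 200 in total, with 1:1 randomisation.

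The Data management and analysis section then sets the analysis population: "The analysis of efficacy will be performed in accordance with the intention-to-treat principle". Missing values are to be filled by last observation carried forward (LOCF).

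**The concern.** An allowance for dropout should leave the required number after the losses have occurred. The figure of 17 looks like 20% of the 83 who are meant to remain, rather than 20% of the 100 who are enrolled. If so, 80% power, 20% dropout and 200 participants cannot all hold on the section's own reasoning, which treats dropouts as reducing the number available. At stake is whether the published justification of the sample size is true as stated, and how much power it overstates.

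**Working it through.** **Inputs** (Sample size calculation, unless noted): response rates 0.91 and 0.75, so a difference of 0.16; α = 0.05; β = 0.2; 83 per group before dropout; 20% dropout; 17 added per group; 200 in total. Allocation is 1:1 (Randomization and allocation concealment). Sidedness is not stated.

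**1. Reproducing 83.** Two-sided comparison of two proportions with unpooled variance:

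n = [p1(1 − p1) + p2(1 − p2)] × (1.960 + 0.842)² / (p1 − p2)²

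= (0.91 × 0.09 + 0.75 × 0.25) × (2.802)² / 0.16² = 82.6, rounded up to 83.

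This matches the plan. One-sided calculations give 66 (unpooled), 68 (pooled) or 80 (pooled with continuity correction). None gives 83, so a two-sided test is inferred.

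**2. The allowance.**

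- As done: 0.20 × 83 = 16.6, rounded up to 17; equivalently 83 × 1.2 = 99.6, so 100 per group.
- As needed: 83 / (1 − 0.20) = 103.75, so 104 per group, 208 in total. That is 21 more per group, not 17.
- Shortfall: 4 per group, 8 in total.
- Remaining after 20% loss from 100: 100 × 0.80 = 80.
- Dropout that 100 per group can absorb: (100 − 83) / 100 = 17%.

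**3. Power at 80 and at 83 per group** (91% v 75%, two-sided 0.05):

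| Method | n = 80 | n = 83 |
|---|---|---|
| Unpooled normal (the formula that yields 83) | 78.7% | 80.2% |
| Exact power of the Pearson chi-squared test | 78.4% | 80.2% |
| Arcsine | 79.1% | 80.5% |
| Pooled normal | 77.4% | 78.9% |

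The unpooled line is power = Φ(0.16 / √(0.2694 / n) − 1.960), where 0.2694 = 0.0819 + 0.1875. At n = 80 this is Φ(0.797) = 78.7%. All four methods put 80 per group below 80% power. The pooled method is already below 80% at 83, so part of its gap comes from the choice of formula rather than the dropout step. Moving from 83 to 80 costs 1.4 to 1.8 points, depending on the method.

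**4. All 100 per group analysed.** If dropouts respond at the assumed rates, power is 86.9% (unpooled), 87.3% (exact), 87.2% (arcsine) or 85.9% (pooled).

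**The case against.** The strongest reply is that 80 per group is not the planned analysis size. Under intention-to-treat with LOCF nobody leaves the efficacy analysis, so 100 per group are compared and power may be well above 80%. This stands, and it confines the 78–79% figure to completers. It does not rescue the sentence, because an allowance for dropout only makes sense if dropouts are taken to be lost, and on that reading 17 is the wrong number.

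A second reply is that the loss is trivial beside the softness of the inputs. The 91% rests on expert experience and the 75% is approximate. With 80 per group and the unpooled formula, a buspirone rate of 74.5% gives 80.8% power and a rate of 76% gives 74.2%. Half a point in an approximate input offsets the whole error. This also stands. It limits the weight of the point, not its correctness.

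A reader might be tempted to go further and count every dropout as a non-responder. The rates become 0.91 × 0.8 = 72.8% and 0.75 × 0.8 = 60%, and exact power with 100 per group is 48.6%. The arithmetic is right, but this is not the protocol's rule. LOCF keeps the last recorded value, so a participant who had responded by week 1, 2 or 4 and then left would still count as a responder. Some dilution is possible, but the article gives nothing from which to size it. Nor does it leave open how missing values are handled, since it names both intention-to-treat and LOCF.

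**Conclusion.** Wrong as written. The dropout step multiplies by 1.2 where it should divide by 0.8, so 100 per group covers 17% dropout, not 20%. Four more per group would be needed to keep 83 at 20%. Among completers at 20% dropout, power is about 78–79%, some 1 to 2 points below the stated 80%.

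This rests on a two-sided test (inferred from the match to 83), on the assumed rates of 91% and 75%, and on the response-rate comparison for which the section calculates.

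A reader might infer that the trial as planned misses 80% power. The documents do not support that. In the planned intention-to-treat analysis with LOCF all 100 per group count, and power for this comparison is about 87% if dropouts respond at the assumed rates and lower if they respond less. The article does not say how dropouts are expected to respond. The finding is a small error in the stated justification, with no consequence for the design.

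**What to change.** Keep 200 participants and restate the sentence, for example:

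*With 100 per group, 83 evaluable participants per group are retained at up to 17% dropout; at 20% dropout, 80 per group remain and power among completers is about 78–79%.*

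Enrolling 104 per group (208 in total) would also make the stated figures agree, but a gain of 1 to 2 points among completers hardly calls for it.

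The cost is one corrected sentence, in which the stated dropout allowance or power becomes slightly less favourable. Enrolment, randomisation and the analysis plan stay as they are.

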### Data management and analysis

CRFs will be entered by two independent researchers and supervised by a third one to ensure accuracy. Data analysis will be performed by statisticians who are blind to the randomization by using SPSS (Statistical Product and Service Solutions) Statistics for Windows, version 20.0 (IBM Corp., Armonk, NY, USA). Continuous variables will be presented as mean and standard deviation, and categorical variables will be presented as frequency or percentage. Demographic data and outcome measurements at baseline will be listed to ensure relatively even baseline levels. A *t* test (if normally distributed) or non-parametric test (if not normally distributed) will be used for continuous variables when conducting baseline comparisons. The repeated measures ANOVA (analysis of variance) will be used when analyzing the primary and secondary outcomes. Chi-squared or non-parametric test will be applied for categorical variables. The analysis of efficacy will be performed in accordance with the intention-to-treat principle. Missing values will be imputed by the last observation carried forward method. Subgroup analysis will be conducted if necessary. A *P* value of less than 0.05 will be considered statistically significant. A mixed-effects model for repeated measures will be performed as a sensitivity analysis of the primary efficacy outcome.

Mid-term date analysis will be conducted after half of the recruitment is finished, and the principal investigator will decide whether any measure should be taken in light of the results. All of the data will be deposited in the platform developed by our team. Anding Hospital will be responsible for the data, and other researchers can have access to the data only after application and permission.

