### Participant recruitment

A total of 200 eligible participants will be recruited from four hospitals in different parts of China: Beijing Anding Hospital, Xiamen Xianyue Hospital, Tangshan 5th Hospital, and Zhumadian 2nd People’s Hospital. Both inpatients and outpatients will be screened for participation from November 2017.

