### Criteria

#### Inclusion criteria

Participants meeting all of the following criteria will be enrolled: (1) inpatients or outpatients with GAD diagnosed in accordance with the International Classification of Disease-10; (2) those with a diagnosed TCM pattern of liver-qi stagnation transforming into fire, which usually manifests as irritability, constriction in the chest, hypochondriac distention, gastric discomfort with acid regurgitation, dry mouth or bitter taste in the mouth (or both), constipation, headache, conjunctival congestion, tinnitus, reddened tongue with yellow fur, and rapid pulse; (3) ages between 18 and 65 (no limitation on gender); (4) Hamilton Anxiety Rating Scale (HAM-A) scores between 14 and 39 (inclusive) at screening and baseline; and (5) written informed consent obtained either personally or by proxy.

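### Baseline HAM-A is listed and tested between arms instead of being named as a covariate, which gives up precision and leaves chance imbalance uncorrected or over-corrected

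*Protocol article*

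**What the plan says.** The Data management and analysis section gives baseline values two roles. They are tabulated for a stated purpose: "Demographic data and outcome measurements at baseline will be listed to ensure relatively even baseline levels". They are also tested between arms: a t test or a non-parametric test, depending on normality, "will be used for continuous variables when conducting baseline comparisons". The section does not say what follows from the result of such a test.

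The same section names repeated measures ANOVA for the primary and secondary outcomes and a mixed-effects model for repeated measures as a sensitivity analysis of the primary outcome. No covariate or centre term is named for either. The Outcome measurements section schedules assessments at screening, baseline and weeks 1, 2, 4 and 8, but the article does not say whether baseline enters the ANOVA as one of its time levels.

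Two other places bear on the point. Participants must have HAM-A "scores between 14 and 39 (inclusive) at screening and baseline", so baseline HAM-A is recorded for everyone. Participants "will be recruited from four hospitals in different parts of China", and the Randomization and allocation concealment section describes no stratification by centre.

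**The concern.** Listing baseline values describes balance; it cannot ensure it. A significance test at baseline asks whether a difference could have arisen by chance, although randomisation already guarantees that any difference did. Whatever its P value, the test leaves the treatment estimate unchanged. The plan therefore assigns to tabulation and testing a task that only the analysis model can do.

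There are two consequences. First, any variation in later HAM-A that baseline HAM-A could explain stays in the error term, so the comparison is noisier than it need be. Second, a chance baseline difference passes into the estimate if only post-baseline scores are compared, or is subtracted in full, which is too much, if the test works like a change score. In addition, if adjustment is left open until the baseline P values are known, the choice of model can come to depend on the data.

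**Working it through.** **The plan's own figure.** The Sample size calculation section uses response rates: "A response rate of 91% for SGQR was assumed", against about 75% for buspirone. It then states: "In the setting of α = 0.05 and β = 0.2, the sample size was calculated to be 83 in each group". The two-sided unpooled normal formula gives

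n = (1.96 + 0.8416)² × (0.91 × 0.09 + 0.75 × 0.25) / (0.91 − 0.75)² = 7.849 × 0.2694 / 0.0256 = 82.6, so 83 per arm.

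The figure reproduces. It rests on response rates and not on HAM-A means, so the present point does not change it. I use 83 below only as a reference number per arm, and the 100 per arm to be randomised for baseline imbalance.

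**Assumed inputs.** The documents give no HAM-A SD, no baseline-to-outcome correlation r and no centre effect. I take r = 0.3, 0.5 and 0.7, work in SD units, and assume equal SD at baseline and at the later visit.

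**Variance factors for a single-visit comparison**, relative to an unadjusted post-baseline score:
- post-baseline score only: 1
- change from baseline, which is how a group-by-time contrast works when baseline is a time level: 2(1 − r)
- baseline as covariate: 1 − r²

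| r | Post score | Change score | Adjusted | Cut vs post score | Cut vs change score |
|---|---|---|---|---|---|
| 0.3 | 1 | 1.40 | 0.91 | 9% | 35% |
| 0.5 | 1 | 1.00 | 0.75 | 25% | 25% |
| 0.7 | 1 | 0.60 | 0.51 | 49% | 15% |

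The last column is 1 − (1 − r²)/[2(1 − r)] = 1 − (1 + r)/2. Adjustment never does worse: 1 − (1 − r²) = r² ≥ 0, and 2(1 − r) − (1 − r²) = (1 − r)² ≥ 0.

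**What this means for power.** Take the effect that has 80% power unadjusted with 83 per arm: d = 2.80 × √(2/83) = 0.435 SD. This is an illustration, not a figure from the plan. Power is Φ(2.80/√factor − 1.96):

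| r | Post score | Change score | Adjusted |
|---|---|---|---|
| 0.3 | 80.0% | 65.8% | 83.6% |
| 0.5 | 80.0% | 80.0% | 89.9% |
| 0.7 | 80.0% | 95.1% | 97.5% |

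For the precision of an unadjusted post score with 83 per arm, the adjusted comparison needs 76, 63 and 43 per arm (83 × 0.91, 0.75 and 0.51, rounded up).

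**Chance imbalance.** With 100 per arm the baseline difference has standard error √(2/100) = 0.141 SD, so its 95% range is about ±0.28 SD. Given a difference of 0.28 SD, the shift in the treatment comparison is r × 0.28 for a post score, (r − 1) × 0.28 for a change score, and zero after adjustment:

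| r | Post score | Change score | Adjusted |
|---|---|---|---|
| 0.3 | +0.08 | −0.20 | 0 |
| 0.5 | +0.14 | −0.14 | 0 |
| 0.7 | +0.20 | −0.08 | 0 |

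**Centre.** If centre explains 1%, 5% or 10% of the outcome variance, removing that share takes 83 per arm to 83, 79 or 75 (83 × 0.99, 0.95 and 0.90, rounded up).

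**The case against.** The strongest objection is that the article is condensed. It names model families without listing their terms, and it nowhere says that the models are unadjusted. A reader might infer that the primary analysis certainly ignores baseline. The documents do not support that, because an analysis plan that is not shown may name the covariate. What stands regardless is the stated text: the article does say how baseline is handled, and the handling it gives cannot do what it is said to do.

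A second objection is that repeated measures ANOVA may already use baseline as a time level. If so, it is wrong to call an imbalance simply uncorrected. This is right, and it changes the description but not the conclusion: the group-by-time contrast then over-corrects and remains less precise than covariate adjustment.

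Third, an unadjusted comparison is unbiased under randomisation, and its standard error already allows for chance imbalance. That stands in full. The loss is one of efficiency, not validity.

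Fourth, the size of the gain depends on r and on which form of the ANOVA is meant, and the documents fix neither. This also stands, so no single power gain can be claimed. A reader might take the permitted HAM-A range of 14 to 39 as proof that baseline is a strong predictor; an eligibility range says nothing about correlation with later scores.

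Finally, a reader might conclude that the four hospitals make a centre term necessary. Since no stratification by centre is described and no centre effect is given, the design does not oblige one.

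**Conclusion.** The point holds as a matter of precision and of a misdescribed safeguard. Listing and testing baseline values neither ensures nor repairs balance, and naming baseline HAM-A as a covariate is better under either reading of the ANOVA. For r between 0.3 and 0.7 the variance reduction runs from 9% to 49% against post-baseline scores and from 35% down to 15% against a change score; at r = 0.5 it is 25% on both readings. These figures rest on assumed correlations, equal SDs and a single-visit comparison. Only the direction of the gain is independent of r. The point does not show that the planned analysis is invalid, that the sample size is wrong for this reason, or that adjustment has been ruled out. The change is worth making because the data are already collected. A centre term would probably add little.

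**What to change.** - State that the primary model analyses post-baseline HAM-A with baseline HAM-A as a continuous covariate, and that baseline is not also a time level.
- Specify the same covariate in the mixed-model sensitivity analysis.
- For HAMD-17 and the TCM Syndrome Scale, use the matching baseline value in the same way.
- Replace the baseline significance tests with a descriptive table by arm, and drop the claim that it ensures balance.
- Optionally add centre as a four-level factor, decided in advance.

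No further data or participants are needed. The cost is a change of wording and the written application to the research ethics committee that the Ethical issues section requires for protocol changes. It should be settled before unblinding. Because a mid-term analysis is planned after half of recruitment, the amendment should record whether results by arm had been seen when the covariate was fixed.

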## Background

Generalized anxiety disorder (GAD) is a persistent and common disorder characterized by feelings of threat, restlessness, irritability, sleep disturbance, tension, and symptoms such as palpitations, dry mouth, and sweating [1]. An epidemiological study in China suggested that the illness has a lifetime prevalence of 0.3% and a 12-month prevalence of 0.2% (the highest prevalence is in the 50- to 64-year-old group) but shows no gender difference [2]. The high prevalence of concurrent psychiatric disorders makes the diagnosis of GAD difficult, possibly contributing to the different epidemiological results of China, Europe, and the US [3, 4]. Comorbidity with at least one other mental disorder at some point troubles the majority of patients with GAD, most commonly with major depressive disorder [1, 5]. Besides, GAD is associated with considerable economic costs owing to work productivity loss and high medical resource use. The role impairments of pure GAD are similar in magnitude to those of major depressive disorder [5].

GAD has a relapsing course, and treatments rarely result in complete resolution of symptoms. In the short to medium term, effective intervention includes psychological therapies, such as cognitive behavioral therapy; self-help approaches based on cognitive behavioral therapy principles; and pharmacological treatments [1]. Until the mid-1980s, pharmacological treatment options consisted primarily of benzodiazepines, which later became an effective short-term therapy in consideration of their abuse potential. For patients requiring long-term treatment, buspirone and some newer antidepressants became the alternatives. Nevertheless, the mild efficacy combined with a slow onset of action dampened the satisfaction with buspirone, whereas antidepressants, mainly selective serotonin reuptake inhibitors (including paroxetine), brought both efficacy and lots of adverse effects [6]. The search for the ideal anxiolytic has never stopped.

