Drugs and placebos covering the whole course of treatment for each participant will be packed uniformly and individually. In each center, there will be a pharmacist responsible for dispensing the prescription. At every visit, participants will receive the drugs scheduled for the next intervention period, and the drugs left from the previous period will be returned. The dosage will be explained to the participants orally and in writing and also recorded in a medical booklet. Medication compliance will be calculated accordingly. The scheduled duration of treatment is 8 weeks unless a serious adverse event happens or the participant quits. Non-pharmacologic care is permitted but other psychiatric medication is prohibited. Administration and dosage of concomitant medication for physical conditions will be permitted and recorded in detail.

Any question raised by the participants will be answered to promote completion. The detailed study schedule is listed in Fig. 2.

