### Outcome measurements

Outcome measurements are scheduled at screening, baseline, and the end of weeks 1, 2, 4, and 8.

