#### Primary outcome

HAM-A, which is one of the first and most widely used rating scales to measure the severity of anxiety symptoms, will be set as the primary outcome [7]. There are 14 items in the HAM-A, which incorporate groups of symptoms (such as fears, autonomic symptoms, and respiratory symptoms) rather than specific, single symptoms. Each item is rated from 0 to 4; the higher the score, the worse the situation. The good reliability and validity of HAM-A make it a standard interviewer-administered instrument [8].

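### The primary HAM-A analysis is fixed as repeated measures ANOVA without a deciding effect or a primary visit, and neither of its standard tests estimates the week-8 difference

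*Protocol article*

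**What the plan says.** The Primary outcome section says that HAM-A "will be set as the primary outcome". It gives no visit, change score or response definition. On timing, the Outcome measurements section says: "Outcome measurements are scheduled at screening, baseline, and the end of weeks 1, 2, 4, and 8". None of these visits is marked as primary. On treatment length, Interventions says: "The scheduled duration of treatment is 8 weeks unless a serious adverse event happens or the participant quits".

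The method is in Data management and analysis: "The repeated measures ANOVA (analysis of variance) will be used when analyzing the primary and secondary outcomes". The same section adds: "Missing values will be imputed by the last observation carried forward method", "A *P* value of less than 0.05 will be considered statistically significant" and "A mixed-effects model for repeated measures will be performed as a sensitivity analysis of the primary efficacy outcome". The mixed model, like the ANOVA, comes without a visit or a contrast.

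The Sample size calculation uses response rates of 91% and 75%. Response is not defined there and is not tied to a visit.

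**The concern.** A two-group repeated measures ANOVA does not give one answer. Its standard output holds a group effect, which compares the arms on their average over the visits entered, and a group-by-time interaction, which asks whether the mean profiles differ in shape in any direction. With baseline and weeks 1, 2, 4 and 8 entered, the interaction has (2 − 1) × (5 − 1) = 4 degrees of freedom. Neither is the difference at the end of treatment.

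Three things are at stake. The primary question has two candidate P values and no rule for choosing between them. Neither comes with an effect size that a clinician can read as benefit after 8 weeks. And a positive result may describe a difference that has gone by week 8. That pattern is conceivable here, because the Background says of the comparator that "the mild efficacy combined with a slow onset of action dampened the satisfaction with buspirone".

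**Working it through.** **The plan's own figure.** With two-sided α 0.05, power 80% and unpooled variance: n = (1.96 + 0.842)² × (0.91 × 0.09 + 0.75 × 0.25) / 0.16² = 82.6, so 83 per group. The stated figure reproduces. It is sized for a comparison of proportions and gives no power for any repeated measures effect.

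**Inputs.** From the article: 100 per arm and the visits baseline and weeks 1, 2, 4 and 8. Assumed, because the article gives none of them: SD, correlations and mean profiles. The effect of 0.44 SD is borrowed from the planning rates, whose arcsine effect size is 2·asin√0.91 − 2·asin√0.75 = 0.438. It sets a scale only and is not a HAM-A estimate.

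**A benefit that grows evenly by visit** (0, 0.11, 0.22, 0.33, 0.44 SD), baseline-to-week-8 correlation 0.5. For equal correlations the power of each one-degree-of-freedom test is about Φ(d/s × √50 − 1.96), where d is the true difference and s the SD of the quantity tested:

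- Group effect, five visits: d = 1.10/5 = 0.22; s = √[(1 + 4 × 0.5)/5] = 0.775; power 52%.
- Group effect, post-baseline only: d = 1.10/4 = 0.275; s = √[(1 + 3 × 0.5)/4] = 0.791; power 69%.
- Week 8 unadjusted: d = 0.44; s = 1; power 88%.
- Week 8 adjusted for baseline: d = 0.44; s = √(1 − 0.5²) = 0.866; power 95%.

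Simulation under equal and under time-decaying correlation gives:

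| Test | Power |
|---|---|
| Group effect, baseline included | 42–50% |
| Group effect, post-baseline only | 57–68% |
| Group-by-time (Greenhouse-Geisser) | 79–86% |
| Week 8, unadjusted | 87–88% |
| Week 8, baseline-adjusted | about 95% |

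Going from group-by-time to the adjusted contrast gains 95 − 79 = 16 or 95 − 86 = 9 percentage points. Of this, 7 to 8 points (95 − 88 or 95 − 87) come from baseline adjustment, which is roughly half or more.

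**A constant 0.44 SD from week 1**, equal correlation. Group effect 89%, group-by-time 90%, unadjusted week 8 88%, adjusted week 8 94%, post-baseline group effect 97.5%. Here averaging does as well as or better than the matching week-8 test.

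**Profiles in HAM-A points** (baseline, weeks 1, 2, 4, 8), assumed SD 7 and correlation 0.5, share of trials significant:

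| True difference | Group | Group-by-time | Week 8 |
|---|---|---|---|
| none | 4.4% | 4.4% | 4.8% |
| 0, −2, −3, −2, 0 | 44% | 87% | 5.4% |
| 0, −3, −4, −2, 0 | 65% | 99% | 4.5% |
| 0, 0, 0, −1, −3 | 18% | 85% | 85% |

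For the second row, as the SD goes from 9 to 5, the group test ranges from 29% to 72% and group-by-time from 65% to 99%. The week-8 test stays near its nominal level.

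**Two tests at 0.05.** If either could be claimed, and treating them as independent, the false-positive rate is 1 − 0.95² = 9.75%. Simulation under the null gives 9–10% with the Greenhouse-Geisser correction.

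**The case against.** The strongest reply is that this is analysis-plan detail. Neither the full protocol nor an analysis plan is shown, and repeated measures ANOVA also allows a comparison within a visit. That stands as a caution: the choice may be written down elsewhere. But the article has itself fixed the test, and the visit and deciding effect are part of what the primary endpoint is. The mixed model does not settle it, since it is a sensitivity analysis and equally unspecific.

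Second, week 8 is nowhere declared the target. It is inferred from the treatment length and the last visit. Given the remark on slow onset, a whole-course or onset question would be legitimate. This stands too. In the early-only profiles the arms truly differ at weeks 1 to 4, so a significant ANOVA there is not a false positive. It answers another question.

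Third, a reader might infer that both ANOVA tests favour early visits, because three of the four post-baseline visits fall by week 4. The omnibus interaction has no such general weighting. Under equal correlation it detects a 0.3 SD difference confined to week 1 in 54.5% of trials and one confined to week 8 in 54.3%. Under decaying correlation the figures are 77% and 68%.

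Fourth, a reader might infer that the plan necessarily dilutes a week-8 benefit. The late-benefit row (85% against 85%) and the constant-effect case contradict that for the interaction, and the constant-effect case contradicts it for the average. The article also does not say that baseline is entered as a repeated level. It could be a covariate, and CGI-I has no baseline level at all.

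**Conclusion.** The point holds in a limited form. The article fixes the primary test but not the effect or visit that decides the trial. By default that leaves two P values and no estimate of the end-of-treatment difference, and either P value can be significant when week 8 shows none. This follows from what the two tests measure and needs no assumption.

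The sizes do rest on assumptions. The averaged group test loses heavily when benefit builds late (42–50% power against 87–88% for an unadjusted week-8 test in the growing profile). The interaction loses little or moderately, and much of its gap to the adjusted contrast is baseline adjustment. With a constant effect the averaged test can be the better one.

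The error rate of about 9% applies only if success may be claimed on either test. The article does not say so; it merely leaves it open. It would be wrong to report this as the plan's actual type I error.

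**What to change.** Before the final analysis, and before anyone sees comparative results, name one primary quantity: the SGQR minus buspirone difference in HAM-A change from baseline to week 8, adjusted for baseline, with its 95% CI, taken as the week-8 contrast of the mixed model already planned. Report weeks 1, 2 and 4 from the same model as secondary results, and keep the repeated measures ANOVA as supportive. If the sponsor instead wants a whole-course effect, it should say so, name that single test, and state whether baseline is a covariate or a repeated level.

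No new data are needed. The costs are that an early-onset advantage becomes a secondary result, and that the mixed model replaces ANOVA with last observation carried forward as the deciding analysis. That needs a protocol or analysis-plan amendment, and the Ethical issues section requires a written application to the ethics committee for protocol changes. Because a mid-term analysis is planned at half of recruitment, the amendment should record whether any comparative data had been seen when the choice was made.
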